## Abstract

**Background:**

In the UK, over 980,000 people are living with dementia, and two-thirds of them live in their own homes. Up to 60% of this population is estimated to be at risk of or already experiencing malnutrition, with 45% facing significant weight loss. As dementia progresses, ensuring that people eat and drink well becomes challenging. Many families affected by dementia access home care services, with home care professionals playing a vital role in supporting and enhancing overall quality of life. Training in identifying nutritional problems and supporting family carers to prevent malnutrition is an identified research need; however, research on the contribution of home care professionals in this area is limited. This study aims to assess the feasibility and acceptability of a nutritional intervention for people living with dementia receiving home care from the perspectives of people with dementia, family carers (dyads), and home care professionals (including home care managers).

**Method:**

This is a mixed-method single-arm feasibility study of a nutrition intervention with embedded process evaluation. Thirty-two participants living with dementia and their carers (dyads) will be recruited from home care organisations providing services for older adults across the South, Midlands, and North of England. The intervention comprises a nutritional awareness training session for home care workers, combined with educational resources for home care professionals, family carers, and friends. It is based on a model of person-centred nutritional care and will be delivered by trained home care professionals in the homes of participating dyads over 4 months. Outcome measures will be collected at baseline and at 4 months.

Analyses will be descriptive and centred on the feasibility and acceptability of the interventions and study procedures. Key feasibility outcomes will include the rate of participant recruitment and dropout, and the percentage of home care staff who adhere to the intervention schedule (setting at least four actions in response to using the resources). Quantitative data analysis will primarily involve descriptive statistics. Acceptability of the intervention will be determined through in-depth semi-structured qualitative interviews conducted with a subsample of participants dyads and home care professionals. An embedded process evaluation will assess intervention implementation, capturing barriers and facilitators through participant interviews.

**Discussion:**

Findings from this study will help inform the development and implementation of a future RCT, should this nutrition intervention be feasible.

**Trial registration:**

NCT05866094.

**Supplementary Information:**

The online version contains supplementary material available at 10.1186/s40814-025-01722-5.

## Background

Over 980,000 people in the UK live with dementia, and this number is predicted to rise to over 2 million by 2050 [1], imposing an annual cost of £26 billion on the UK economy [2]. Poor nutrition significantly contributes to ill-health and stress for people living with dementia and their carers [3]. The management of eating and drinking difficulties has been identified as a research priority [4]. Two-thirds of people with dementia live in their own homes [5], with estimates indicating between 14% [6] and 60% [7, 8] are with or at risk of malnutrition and 20–45% experiencing significant weight loss [3].

While health care professionals like district nurses, practice nurses, and general practitioners (GPs) offer treatment and care to people with dementia in the community, nutritional care may not be prioritised until the point of deterioration, despite the National Institute for Health and Clinical Excellence (NICE) guidance and quality standards [9, 10]. Health care professionals face various barriers to providing nutritional care, including brief and infrequent contacts often related to other conditions (e.g. diabetes clinic, blood tests), organisational culture, lack of fit-for-purpose screening tools, limited knowledge and skills, and poor communication between services [11]. As a result, health care professionals may not be best positioned to identify and manage nutrition-related problems, particularly at an early stage. The responsibility for day-to-day nutritional management predominantly falls on family carers, who often lack information and resources, thereby increasing the risk of nutritional decline for the person living with dementia [12].

There is a need for interventions to improve nutritional care for people with dementia living at home. Many families affected by dementia rely on home/domiciliary care services, with over 400,000 accessing these services across the UK [13]. Most home care, including local authority-funded services, is provided by the independent sector. Home care professionals typically see care recipients more frequently and for longer than health care professionals, and their role may involve supporting eating, drinking, and meal preparation. They are potentially well-placed to identify weight loss, eating and drinking difficulties, reduced nutritional intake, the risk of malnutrition, and to support family carers in delivering nutrition-based interventions. Studies have highlighted the need for home care professionals to receive training and support in identifying nutritional problems and supporting family carers around managing eating, drinking, and preventing malnutrition [14, 15]. Appropriate nutrition and hydration care is a component of the core principles and standards for supporting people living with dementia in health and adult social care [16]. However, research on the contribution that home care professionals might make in this area is limited.

Targeting interventions at home care professionals and family-carer dyads, with input from appropriate health care professionals, may provide a proactive and wide-reaching approach to nutritional assessment and management. Malnutrition and unintentional weight loss in people living with dementia, resulting from reduced appetite and difficulties with eating and swallowing [17, 18], significantly contributes to physical and cognitive decline, reduced quality of life, increased health care utilisation [18, 19], and substantial Health and Social Care expenditure (approximately £23.5 billion annually) [20]. Early identification of nutrition-related health risks and intervening via referral to nutrition support and advice from health care professionals can prevent deterioration and potentially reduce associated health care service costs for treating malnutrition. Early intervention may also alleviate the stress and burden that eating and drinking difficulties impose on family carers, potentially reducing or delaying admission to residential care [21]. Developing an intervention for home care professionals and family carers, aimed at supporting people with dementia living at home, is a crucial step towards improved care and outcomes. This initiative aligns directly with NHS priorities and the NHS Long Term Plan [22] to develop new and effective integrated pathways for better care across health and social care systems.

The Health and Social Care Act 2008 (Regulated Activities) Regulations 2014 (Regulation 14), enforced by the Care Quality Commission (CQC) [23], mandates that provider care organisations assess individuals’ nutritional needs and provide appropriate nutrition and hydration to meet those needs. This regulation forms part of the overarching requirement for providers to deliver safe, effective, and compassionate care. Despite this standard, there remains a need to enhance the delivery of nutritional care. A scoping review (35 studies) on managing the nutritional care of people with dementia at home [24] revealed nutrition-related difficulties leading to inadequate or unbalanced dietary intake and increased malnutrition risks at all stages of the disease. While some beneficial outcomes for nutritional status were observed in intervention groups, the authors identified a need for further research to develop and test acceptable and effective individualised nutritional interventions. In the home care context, a qualitative study [15] exploring the experiences of both health care professionals and home care professionals highlighted the challenges of providing effective care and support, emphasising limited time when supporting people living with dementia and poor knowledge of appropriate food and drink choices. However, the study identified that collaboration between home care professionals and family carers could improve care outcomes. Two European randomised controlled trials (RCTs) [25, 26] involving a nurse- or multi-disciplinary team delivered nutrition intervention for older people at home reported positive effects on quality of life and delayed nutritional decline. In line with recommendations from our research in the care home context [27], the scoping review [24] similarly advocated a whole-systems approach to delivering nutritional care for people living with dementia receiving home care.

This protocol reports the current study (TOMATO: nuTritiOn and deMentia AT hOme), designed with the primary aim to assess the feasibility and acceptability of a nutritional intervention adapted for people living with dementia receiving home care. The study will explore the perspectives of people with dementia, their family carers, and home care professionals (including home care managers).

## Nutritional intervention adaptation

This section briefly outlines the adaptation of the nutritional intervention. The intervention was adapted from our evidence-based care home resource [27, 28] and included dementia training for care staff, based on good practice and as identified in previous research [29], which addressed similar learning, development, and language needs of the workforce.

We utilised the ‘ADAPT guidance’ for adapting interventions to new contexts to tailor the intervention to the home care setting [30]. Insights gathered from qualitative interviews (conducted individually and in pairs) with people living with dementia, their family carers, and homecare professionals informed the refinement of the intervention. This provided a framework based on the model of person-centred nutritional care underpinned by six core factors, and the key principles are summarised in the logic model (see Additional file 2).

Following the Behaviour Change Wheel (BCW) systematically [31], we iteratively conducted the COM-B (Capability, Opportunity and Motivation Behavior) mapping for the nutrition intervention. In line with the recommendations for using the BCW in practice [32, 33], the Acceptability, Practicability, Effectiveness/cost-effectiveness, Affordability, Safety/side-effects, Equity (APEASE) criteria were applied during initial judgments to decide which intervention functions, policy categories and behaviour change techniques (BCTs) were most appropriate.

The mapping led to the identification of five of the six COM-B constructs (Psychological Capability, Physical capability, Social Opportunity, Physical Opportunity and Reflective Motivation), five components of the intervention functions (Education, Training, Enablement, Environmental Restructuring, Modelling), three policy categories (Communication/Marketing, Guidelines, and Environmental/Social Planning) and 12 associated Behaviour Change Techniques (BCTs) based on BCT Taxonomy version 1 [34] [Problem solving, Goal setting (outcome), Action planning, Instruction on how to perform the behaviour, Information about health consequences, Information about social and environmental consequences, Demonstration of the behavior, Prompts and cues, Credible source, Restructuring the physical environment, Restructuring the social environment and Adding objects to the environment]. Comprehensive details about the intervention adaptation process (Phase 1) will be published separately.

Additionally, the intervention adaptation was informed by input from the TOMATO Patient and Public Involvement (PPI) group, with the Project Steering Group (PSG) providing expert and lived experience insight throughout the process. The tailored intervention components consist of home care professionals’ nutrition awareness training and adapted educational resources (detailed and handy guides for home care professionals, family carers and friends) with validated tools (e.g. the Patients Association Nutrition Checklist [35] and simple practical approaches to help improve and support eating and drinking well for people living with dementia receiving home care.

## Objectives

### Primary objectives

Assess the acceptability and feasibility of the nutritional intervention including fidelity and adoption and understand the barriers and facilitators to using the intervention.

### Secondary objectives

Collect data on the cost and resource use of health and social care services during the delivery of the interventionEvaluate the feasibility and acceptability aspects of the research design and procedures (e.g. screening, consent processes, recruitment and attrition rates and potential outcome measures) to help inform the planning and design of a future trial.

## Methods

### Study setting and participants

Thirty-two participants with dementia and their carers will be recruited via four to eight home care organisations that provide services for older adults (with an average of 8 dyads per home care provider), across the South, Midlands, and North of England.

We will advertise the opportunity to participate in this study by speaking at forums attended by home care managers and through direct contact with national home care organisations (with franchises) and smaller independent providers, drawing on the network with which the project team already has an established relationship.

We will work together with the participating home care providers (funded privately or by the local authority) across these regions to ensure variability in demographics, diversity, and local services. The nutrition intervention will take place in participants’ own homes.

### Study design

This is a single-arm, non-randomised feasibility study in which participants living with dementia who use home care services will receive the intervention. A mixed-methods approach will be used to assess the feasibility and acceptability of a nutritional intervention for people with dementia living at home, with an embedded process evaluation. This evaluation will collect data on intervention fidelity and implementation, including barriers and facilitators, to contextualise the findings, and inform a future trial.

The design of this protocol follows the Standard Protocol Items Recommendations for Interventional Trials (SPIRIT) 2013 guidelines (see Additional file 1) [36]. Results will be reported in line with the CONsolidated Standards of Reporting Trials (CONSORT) extension for pilot and feasibility studies [37] and the Template for Intervention Description and Replication (TIDieR) checklist (see Additional file 2) [38]. Implementation and evaluation will be guided by Normalisation Process Theory (NPT) [39], which is underpinned by four key constructs: coherence or sense-making, cognitive participation, collective action, and reflexive monitoring. The NPT focuses on the activities that individuals and organisations need to undertake to integrate and normalise new, complex practices into their daily routines. Additionally, the RE-AIM framework for process evaluations and implementation [40] will be used to report outcomes that will guide future trial planning.

This study is registered with the ClinicalTrials.gov database, trial number NCT05866094.

### Patient and public involvement

The research team established a PPI group of eight members, including people living with dementia, family carers, and home care professionals, with a designated lay PPI lead. Together, they contribute valuable insights informed by their lived experience. They will continue to meet online at key stages throughout the study.

Their valuable input will be represented in the core TOMATO research team meetings, informing the project design, ethics documentation and study delivery. The group will also continue to discuss and review the study's progress, research findings and dissemination activities. Additionally, they will be actively involved in the preparation of public-facing dissemination materials.

### Eligibility criteria

The study eligibility criteria are presented in Table 1. The study participants include (1) people living with dementia who are receiving home care; (2) their family/carers, and (3) home care professionals and managers from the participating home care provider organisations.

**Table 1 Tab1:** Eligibility criteria for people living with dementia, carers and home care professionals

	Inclusion criteria	Exclusion
People living with dementia	• formal diagnosis or functional symptoms associated with probable dementia (assessed by a senior home care staff using the FAST© [41]). • In receipt of home care services • currently at risk of, or experiencing malnutrition (assessed by a senior home care staff using the ‘Patients Association Nutrition Checklist’) [35]. • have family member/friend providing care/support resident in the same house as the person with dementia or living close by. *For interviews, people living with dementia will* • Currently be or have recently been (in last 6 months) at risk of/experienced malnutrition. • Be able to communicate fluently enough in English or provide informed consent with the assistance of a translator or family member to participate. • Be able to recall their experiences of malnutrition.	• At end of life or on an end-of-life care pathway. • Permanently cared for in bed. • Do not have an informal caregiver. • Receiving specialist nutritional support, e.g. feeding via tube.
Carers and home care professionals	• Currently or have recently (in last 6 months) provided care for someone living with dementia at risk of or experiencing malnutrition. • Able to communicate fluently enough in English or provide informed consent to participate with the assistance of a translator or family member.	• Have not recently (in last 6 months) provided care for someone with dementia at risk of/experiencing malnutrition. • Not able to communicate fluently enough in English or provide informed consent.

Functional Assessment Staging Test (FAST) [41] describes seven stages in the progression of Alzheimer’s disease, with good validity and reliability FAST focuses on the ability to perform activities of daily living, delineating the progressive loss of functioning through seven stages (from 1 = normal adult to 7 = severe Alzheimer’s)

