### Outcome measures and data collection

The primary outcome will be an assessment of study feasibility, including acceptability, recruitment and retention, protocol adherence and adaptations, compliance with study procedures including completion of questionnaires, percentage withdrawal, completion of outcomes and assessments, barriers and enablers to intervention delivery. We will relate the evaluation to focused components of feasibility studies [43]. This includes the assessment of acceptability, demand, implementation, practicality, adaptation, integration, and expansion. Secondary outcomes will be collected at baseline and 4-month after the first visit by the home care professional, unless recorded as routine data, at other time intervals. In such cases, all data recorded over the intervention period will be gathered. They will include nutritional status of the person with dementia (body weight, height to calculate Body Mass Index, BMI of < 20 kg/m^2^ as an indicator of undernutrition), quality of life using EQ-5D-5L/EQ-5D-5L-Proxy and DEMQoL/DEMQoL-Proxy [44–46] (as a robustness check and interview administered) and functional status (Deterioration in Daily Living Activities in Dementia) [47] and carer burden using Zarit Burden Interview [48]. Outcome measures were selected based on our logic model and informed by consultation with the PPI and Project Management Group. Table 4 outlines these assessments and strategies for measuring the outcomes of the TOMATO study.

**Table 4 Tab4:** TOMATO outcome measures

Feasibility parameter	How they will be assessed?		When the measures will be collected? [pre- only, post- only, pre and post intervention]
Recruitment rate	Percentage of participants recruited from participating home care provider		Pre and post
Attrition rate	Percentage of participants who drop out of the study before completion		Pre and post
Intervention Adherence	Percentage of staff who adhere to the intervention schedule (including the completion of the monthly action logs for 4 months)		Post-only
Components of focus			
Acceptability	Semi-structured interviews/focus group with participants		Post-only
Demand	Analysis of screening data Semi-structured interviews/focus group with participants		Post-only
Implementation	Documentary analysis Semi-structured interviews/focus group with participants		Post-only
Practicality	Semi-structured interviews/focus group with participants		Post-only

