### Nested process evaluation

As part of the study process evaluation, qualitative data will be generated from semi-structured interviews or focus groups conducted by the researcher at 4 months.

A sample of participants receiving home care and their carers (*n* = 12 dyads) will be invited to participate in semi-structured interviews. Family carers will be given the option to have a separate interview, and paid care for the person with dementia will be offered.

Home care professionals (*n* = 12), and home care managers (*n* = 4) will be invited to take part in an interview or a focus group (in pairs of 2–3 staff per provider organisation). We will adopt blended approaches, incorporating a combination of face-to-face interviews (using a Dictaphone) and online interviews/focus groups (via Zoom/Teams software), which will be video and/or audio-recorded and transcribed verbatim.

We will use a pre-designed topic guide, developed in conjunction with our PPI group consisting of key open-ended questions. Participants will be asked to feed back about various aspects of their experiences to inform a potential future trail including receiving or delivering the nutrition intervention, identifying priority areas, the delivery process, how the approach worked, the barriers, facilitators, and aspects that could be improved. For all participants, we will collect demographic data from home care records, including age range, gender, ethnicity, living arrangements, and dementia diagnosis.

Documentary analysis will be undertaken from a review of care plans of people with dementia (at baseline; during preceding 4-month period and at 4 months) using a checklist of key data, e.g. food and drink intake, weight recording, costs.

A bespoke document will be used to collect data on intervention fidelity and dose. This document will be completed by home care professionals, informal carers, or healthcare professionals, or via standardised recording in care plans. Implementation fidelity will be guided by a revised version of Carroll et al.’s conceptual framework [49].

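### Interviewees with dementia are screened on recall of malnutrition, although the interviews ask about receiving the intervention

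*Protocol article*

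**What the plan says.** All points are from the protocol article.

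- **Enrolment (Eligibility criteria, Table 1).** The person with dementia must be "currently at risk of, or experiencing malnutrition". Being at risk is enough. Under Informed consent, a person who lacks capacity may join on a personal consultee's advice.
- **Interview (same table).** Extra conditions apply to interviewees with dementia. The first accepts risk of malnutrition, now or within the last 6 months, as an alternative to having experienced it. The last is "Be able to recall their experiences of malnutrition".
- **Timing and content (Nested process evaluation).** The qualitative data come from "semi-structured interviews or focus groups conducted by the researcher at 4 months". Topics are the participant's experiences, "including receiving or delivering the nutrition intervention, identifying priority areas", together with how the approach worked, barriers, facilitators and possible improvements.
- **Use.** The abstract states: "Acceptability of the intervention will be determined through in-depth semi-structured qualitative interviews". Under Outcome measures and data collection: "The primary outcome will be an assessment of study feasibility, including acceptability, recruitment and retention, protocol adherence and adaptations", among other elements.

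**The concern.** An interview criterion should select people who can answer the questions that will be put to them. This one selects on memory of malnutrition, which the described topics do not cover. It also sits in the same list as a condition that lets in people who have only been at risk, and who may have nothing of the kind to remember.

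What is at stake is the first-hand account of people with dementia. The article says it will explore their perspectives, and acceptability is to be determined through these interviews. A senior care worker or researcher who applies Table 1 literally would turn away people with something relevant to say about the support they received.

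**Working it through.** The plan attaches no figure to this criterion, so the check is a comparison of the passages, with a little arithmetic for scale.

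1. **Who can be in the study.** At risk or malnourished, with or without capacity to consent (Table 1; Informed consent). No recall of anything is needed.

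2. **Who can be interviewed, among people with dementia.** The exposure condition is met by risk alone. The recall condition refers to experiences of malnutrition. A participant who has been at risk but never malnourished meets the first and, read literally, cannot meet the second, however good their memory.

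3. **What the interview needs.** The ability to say something about the intervention as received over the 4 months.

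4. **Crossing the two abilities.**

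| | Can speak about the support received | Cannot speak about it |
|---|---|---|
| Can recall malnutrition | admitted, informative | admitted, not informative on the intervention |
| Cannot recall malnutrition, or has none to recall | excluded, although informative | excluded |

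 The rule works only if the top-right and bottom-left cells are empty. Nothing in the document suggests that they are, and step 2 shows how the bottom-left cell can fill.

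5. **Who is outside the rule.** Table 1 sets no recall condition for carers or home care professionals. Carers may be interviewed separately, and 12 home care professionals and 4 managers are also to be invited (Nested process evaluation).

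6. **Scale.** The interview sample is 12 dyads.
 - Share of the enrolment target: 12/32 = 37.5%.
 - Share of the dyads hoped for at follow-up: 12/25 = 48%.
 - The number of people with dementia who would fail the recall condition is not given and cannot be derived.

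7. **Timing.** Interviews are described only at 4 months, and Table 4 marks acceptability as post-only. The plan hopes to have 25 of 32 dyads at that point, so 32 − 25 = 7 dyads (7/32 = 21.9%) may have left. The article does not say whether they can be interviewed.

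**The case against.** The best defence is that the rule touches one group of respondents and one component of a broad outcome. Carers and staff can report on participants with severe dementia. Recruitment, retention, adherence and questionnaire completion are measured without the interviews. Study progression criteria also treats data completeness above 80% as evidence of acceptability. All of this stands, and it limits the point. It does not make the bullet fit its purpose: proxies do not replace the person's own account, and completeness measures whether forms were filled in, not what people thought of the intervention.

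A second defence is that experiences of malnutrition may be meant loosely, to include being at risk or having difficulty eating. That would ease the conflict with the at-risk condition, but the rule would still not concern the support received.

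A reader might also infer more than the documents support:

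- **That the primary outcome rests on completers with intact recall.** It does not. It is a composite, and most of its elements come from screening, enrolment, follow-up or staff records.
- **That people who leave early are barred from interview.** This would be an inference from the 4-month timing. The invitation is to "A sample of participants receiving home care and their carers", with no mention of completion. Safety reporting says follow-up continues where possible, reasons for loss are to be assessed, and research staff contact home care professionals through the 4 months. The interview sampling frame may also be set out in the full protocol.
- **That the findings are biased towards approval.** The causes of attrition that the article anticipates are intercurrent illness and falls, not dislike of the intervention. No direction of bias is shown.
- **That the rule contradicts the purposive aim.** The intended spread of dementia severity in Sample size describes the study sample of 32 dyads, not the 12 interviewed.

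**Conclusion.** The point holds in a limited form. The recall bullet does not match the interview's content or the at-risk condition in the same list. Followed literally, it excludes some people with dementia who could speak to acceptability. The effect is confined to their own voice within the acceptability component. Its size is unknown, and no direction of bias can be claimed.

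This rests on two assumptions: that Table 1's interview conditions govern the 4-month interviews, and that the bullet is applied as worded. The single interview time point deserves a clarifying sentence but is not shown to be an error.

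**What to change.** Replace the recall bullet in Table 1 with a criterion tied to what the interview asks, for example: able to talk about the eating and drinking support received, with carer support if wished.

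Optionally, add a sentence under Nested process evaluation saying that dyads and staff who stop early may be invited to interview within the existing numbers. No quota is needed.

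The cost is a small ethics amendment, with no additional interviews. The new wording still selects on the ability to communicate and to remember recent support, so people with more severe dementia may remain under-represented among interviewees. The report should say so.
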